### Statistical power and sample size

2.6

To determine the required sample size, we conducted power calculations using the R package *powerlmm* (Magnusson, 2018). Based on previous meta-analytic evidence for the effectiveness of web-based interventions for BED (Beintner et al., 2014; Haderlein, 2022; Hilbert et al., 2019), we chose medium effect sizes of Cohen's *d* = 0.50 as a benchmark for expected pre-post differences between the intervention group and the waitlist control group. Power calculations using an intraclass correlation of .40 (Arend and Schäfer, 2019), a power of .80, and an alpha level of .05 resulted in a required sample of *N* = 152. Additional power analyses, including possible dropouts of 20% and different intra-class correlation coefficients, can be found in the supplementary material (Fig. S3), strengthening our conclusion that our sample will be sufficiently large to detect a medium effect under different statistical assumptions.

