These strengths have to be set against the limitations. First, due to the relatively high dropout rates of web-based interventions (Linardon et al., 2018; Puls et al., 2020), low adherence might become a problem in the current study. This challenge may particularly apply to our trial design, as regular weekly assessments and intensive longitudinal measures collected in everyday life carry a higher participant burden. To increase motivation and adherence in both groups, participants will be reminded of the study using weekly text messages, regular emails, and phone calls. Moreover, recruiting a large clinical sample of participants fulfilling the criteria for BED is necessary to achieve adequate statistical power. However, BED is still under-recognized (Brownley et al., 2016, Coffino et al., 2019, Cossrow et al., 2016, Kazdin et al., 2017, Keski-Rahkonen, 2021, Silén et al., 2021) as it represents a relatively new diagnosis introduced in the DSM-5 (APA, 2013) and the eleventh revision of the International Classification of Diseases (ICD-11; Reed et al., 2019). Therefore, knowledge concerning the condition among healthcare providers and the general population remains scarce (Keski-Rahkonen, 2021; Venkatesh et al., 2021). To ensure the necessary sample size, we will allow participation from different countries (if subjects have sufficient German language skills) and employ a broad range of recruitment methods, including social media posts, email distributors, flyers in healthcare settings, and waitlists of patients with BED, which will enhance the chances of achieving the required sample size.

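### N = 152 holds no allowance for dropout: at the planning ICC of .40, the 20% dropout named in section 2.6 lowers power from 80% to about 73–75%, so the sufficiency claim is not supported there

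*Protocol article*

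**What the plan says.** Section 2.6 (Statistical power and sample size) sets the effect as follows: "we chose medium effect sizes of Cohen's *d* = 0.50 as a benchmark for expected pre-post differences between the intervention group and the waitlist control group". The remaining inputs are given as "Power calculations using an intraclass correlation of .40 (Arend and Schäfer, 2019), a power of .80, and an alpha level of .05", and these "resulted in a required sample of *N* = 152". The abstract gives the same 152 as the number to be randomly allocated, so nothing is added for dropout between the calculation and recruitment.

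The section then turns to robustness: "Additional power analyses, including possible dropouts of 20% and different intra-class correlation coefficients, can be found in the supplementary material (Fig. S3"). It describes these analyses as "strengthening our conclusion that our sample will be sufficiently large to detect a medium effect under different statistical assumptions".

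Elsewhere the article treats dropout as a real prospect without giving a figure. Section 2.5.2 calls it notable in earlier studies, and section 3.1 warns of low adherence "due to the relatively high dropout rates of web-based interventions".

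**The concern.** A sample size solved as the minimum for 80% power has no slack. If 152 is that minimum for complete data, any dropout lowers power below the target, and so does any ICC below the planning value. Analyses with 20% dropout and different ICCs would then show that the 80% depends on complete data or a more favourable ICC, and would not reinforce the conclusion in general.

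What is at stake is how a null result is read. A reader who takes section 2.6 at face value will assume a 20% risk of missing a true medium effect. If a fifth of participants are lost, that risk at the planning ICC is about 25–27% in the mixed model and about 29% among completers.

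**Working it through.** **Inputs**

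- Section 2.6: total N 152; d = 0.50 as the between-arm difference in pre-post change, in units of the baseline SD (total variance 1); ICC .40, so residual variance 0.60; power .80; alpha .05. Sidedness is not stated, and two-sided is assumed because it reproduces the plan's N. A one-sided test at the same N would give about 88%.
- Section 2.3.1: 1:1 allocation, so 76 per arm.
- Section 2.5.1: three assessments (0, 6 and 12 weeks, coded t = 0, 0.5, 1), random intercepts, test of the treatment × time interaction.

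**Step 1. Reproduce the plan's figure with complete data.**

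Variance of one person's slope = (1 − ICC)/Σ(t − t̄)² = 0.60/0.5 = 1.2.

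n per arm = 2(1.96 + 0.8416)² × 1.2/0.50² = 2 × 7.849 × 1.2/0.25 = 75.4, rounded up to 76, so N = 152.

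Power at 76 per arm: SE = √(2 × 1.2/76) = 0.1777; 0.50/0.1777 = 2.814; Φ(2.814 − 1.96) = .803 (.798 by the noncentral t). The plan's N is reproduced exactly with zero dropout.

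**Step 2. Apply 20% dropout at ICC .40, using every observed visit.**

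For a person with k observed visits, the information on (intercept, slope) is X′V⁻¹X, where V has 1 on the diagonal and .40 off it:

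- three visits: [[1.667, 0.833], [0.833, 1.250]]
- two visits: [[1.429, 0.357], [0.357, 0.298]]
- one visit: [[1, 0], [0, 0]]

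Take 10% lost before week 6 and a further 10% before week 12, equally in both arms. The weights are 0.8, 0.1 and 0.1, and the average information is [[1.576, 0.702], [0.702, 1.030]]. The slope variance is 1.576/(1.576 × 1.030 − 0.702²) = 1.395 (unrounded entries). Then SE = √(2 × 1.395/76) = 0.1916; 0.50/0.1916 = 2.609; power = Φ(0.649) = .742.

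| Timing of the 20% loss | Slope variance | Power, normal | Power, t |
|---|---|---|---|
| 10% before week 6, 10% before week 12 | 1.395 | .742 | .737 |
| All before week 6 | 1.408 | .738 | .733 |
| All between weeks 6 and 12 | 1.383 | .746 | .740 |

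Completers only: 76 × 0.8 = 60.8 per arm; SE = √(2 × 1.2/60.8) = 0.1987; 0.50/0.1987 = 2.517; power = Φ(0.557) = .711.

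**Step 3. Effect detectable with 80% power.**

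All available data: 2.8016 × 0.1916 = 0.54. Completers: 2.8016 × 0.1987 = 0.56.

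**Step 4. Vary the ICC at N = 152** (normal/t; dropout as in the first row above).

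| ICC | Complete data | 20% dropout |
|---|---|---|
| .20 | .683/.678 | .625/.620 |
| .30 | .741/.735 | .679/.674 |
| .40 | .803/.798 | .742/.737 |
| .50 | .869/.865 | .813/.808 |
| .60 | .931/.928 | .887/.883 |

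At ICC .50 with 20% dropout, power lies between .803 and .817 across the three timings and both approximations.

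**Step 5. Size of the gap in participants.**

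At ICC .40 with 20% dropout, 80% power would need about 174–180 in total with the mixed model, or 152/(1 − 0.20) = 190 by simple inflation.

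**The case against.** The strongest reply has four parts.

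- **Fig. S3 was not seen.** Its ICCs, dropout timing and slope variance are unknown. This stands: nothing here shows that the figure is wrong. What can be tested is whether the sentence in section 2.6 follows from the inputs printed beside it, and at the planning ICC it does not.
- **Different assumptions does not mean all assumptions.** This partly stands. At ICC .50 or .60 the sample is sufficient with 20% dropout. Section 2.4.4 also cites a test-retest reliability of .84 for the binge-eating measure. That is not the correlation across this trial's 12 weeks, but it gives no reason to think a low ICC the likelier departure. A reader might infer that N = 152 reaches 80% only with zero dropout whatever the ICC; that is true at .40 and false from about .50 upward.
- **20% is a scenario.** This stands. Section 2.6 calls it possible, sections 2.5.2 and 3.1 give no rate, and section 3.1 lists reminders meant to limit the problem. A reader might infer that the plan expects 20% dropout and so has knowingly underpowered the trial; the text does not support that. The loss of power is conditional on the scenario.
- **The shortfall is modest.** Power falls 5 to 7 points, and d of about 0.54 is still close to a medium effect. This bears on severity. It does not rescue the wording, because .80 is the only standard of sufficiency the section gives.

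**Conclusion.** The point holds at the planning ICC. N = 152 is correctly calculated for 80% power with complete data and contains no dropout allowance. With 20% dropout and ICC .40, power is about 73–75% (about 71% for completers). It is also below 80% without dropout if the ICC is lower, about 74% at .30. The target is kept with 20% dropout only for an ICC of about .50 or more. The claim that these scenarios strengthen the case for a sufficiently large sample is therefore unsupported at the plan's own ICC.

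The result assumes a two-sided test, equal dropout in both arms, an effect standardised to the baseline SD, and no between-person variation in slopes. Slope variance would lower power further; a value of 0.10 gives about 77% even without dropout. The timing of dropout barely matters.

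This is a should-fix restatement of power. No estimate, test or error rate changes.

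**What to change.** Replace the general sufficiency claim in section 2.6 with the power under each scenario, for example:

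> N = 152 gives 80% power for d = 0.50 with complete data and an ICC of .40. With 20% dropout, power is about 73–75% (about 71% for completers). With 20% dropout, 80% is retained only for an ICC of about .50 or more.

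State that the test is two-sided, if it is, and reconcile the new wording with Fig. S3, giving the dropout pattern and ICCs used there. If Fig. S3 rests on different assumptions, print them and the resulting power.

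Do not quote the higher power of a baseline-constrained analysis here unless the primary model in section 2.5.1 is changed to that analysis; otherwise the figure would describe an analysis that is not planned.

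The cost is a few sentences and a slightly less favourable stated power. No patients are added and the design is unchanged.

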## Discussion

3

BED is the most prevalent eating disorder and is associated with marked impairments in physical health, social integration, professional performance, and quality of life (Ágh et al., 2015; Erskine et al., 2016; Stice et al., 2009; Udo and Grilo, 2020). Nevertheless, treatment rates for BED are lower than for many other mental disorders, including eating disorders, such as anorexia nervosa and bulimia nervosa (Coffino et al., 2019, Hay et al., 2020, Kessler et al., 2013, Silén et al., 2021, Smink et al., 2013). Consequently, improving access to specialized treatment and decreasing barriers in the help-seeking process is an important goal to reduce the burden of illness and chronicity in BED.

Web-based interventions can reduce these barriers and facilitate access to evidence-based treatment for patients with BED (Aardoom et al., 2013; Dölemeyer et al., 2013; Venkatesh et al., 2021). However, despite the increasing number of empirical studies investigating web-based self-help for depression and anxiety symptoms (for a meta-analysis, see Spek et al., 2007), there is still a scarcity of high-quality studies on the effectiveness of online interventions for BED (Haderlein, 2022). Therefore, examining how and whether these programs successfully treat BED when implemented in health care systems remains an important avenue for future research. Building on previous research of technology-based eating disorder interventions (Beintner et al., 2014; Haderlein, 2022), the present study aims to evaluate the effectiveness of a web-based CBT intervention for BED in routine care settings.

### Strengths and limitations of the study

3.1

We highlight five major strengths of this trial. First, the two-armed randomized controlled design provides a high degree of internal validity, allowing to attribute observed group differences to the web-based intervention with sufficient certainty. Second, the 12-week waiting period for the intervention was chosen to maximize our findings' generalizability and external validity. As such, a waiting time of three months closely reflects care reality for patients with BED in Germany, as awaiting outpatient psychotherapy requires, on average, three to six months (BPtK, 2018). Third, investigations of improvements in well-being and quality of life following web-based interventions remain scarce. To address this gap, we will assess crucial secondary outcome parameters such as changes in self-esteem and work capacity to evaluate whether web-based interventions can improve BED patients' overall daily life experiences apart from symptom reduction. Fourth, according to recent methodological recommendations (Hesser, 2015), our statistical analysis will use a linear mixed models framework. This approach has several advantages over traditional analysis methods, as it allows considering the nested data structure and has more power when handling missing data. Finally, to increase the validity of our findings, the structured diagnostic interviews will be conducted by independent researchers who are blind to treatment conditions. Moreover, biases associated with retrospective assessments will be reduced by closely tracking symptom fluctuations over the study period. To achieve this goal, we will combine classic self-report instruments with weekly reports of eating disorder symptoms (Munsch et al., 2007; Munsch et al., 2019) and naturalistic EMA to obtain a high temporal resolution and ecological validity of measures.

These strengths have to be set against the limitations. First, due to the relatively high dropout rates of web-based interventions (Linardon et al., 2018; Puls et al., 2020), low adherence might become a problem in the current study. This challenge may particularly apply to our trial design, as regular weekly assessments and intensive longitudinal measures collected in everyday life carry a higher participant burden. To increase motivation and adherence in both groups, participants will be reminded of the study using weekly text messages, regular emails, and phone calls. Moreover, recruiting a large clinical sample of participants fulfilling the criteria for BED is necessary to achieve adequate statistical power. However, BED is still under-recognized (Brownley et al., 2016, Coffino et al., 2019, Cossrow et al., 2016, Kazdin et al., 2017, Keski-Rahkonen, 2021, Silén et al., 2021) as it represents a relatively new diagnosis introduced in the DSM-5 (APA, 2013) and the eleventh revision of the International Classification of Diseases (ICD-11; Reed et al., 2019). Therefore, knowledge concerning the condition among healthcare providers and the general population remains scarce (Keski-Rahkonen, 2021; Venkatesh et al., 2021). To ensure the necessary sample size, we will allow participation from different countries (if subjects have sufficient German language skills) and employ a broad range of recruitment methods, including social media posts, email distributors, flyers in healthcare settings, and waitlists of patients with BED, which will enhance the chances of achieving the required sample size.

### Conclusion

3.2

Bridging the gap between current knowledge about effective BED treatments and available interventions in clinical care is critical for advancing healthcare for this condition. The present randomized controlled trial aims to address this gap by testing whether providing low-threshold access to a web-based intervention for BED in routine care may help patients reduce their core symptomatology and improve their emotional and social well-being. Our findings will thus address the scarcity of studies evaluating the effectiveness of web-based interventions for eating disorders in standard healthcare settings (e.g., Vollert et al., 2019). Finally, to better understand which patients particularly benefit from web-based programs, our randomized controlled trial is designed to test individual treatment trajectories and mechanisms of change. Understanding for whom and why these interventions reduce eating disorder symptoms is essential to providing more targeted, ultimately more effective BED treatments. When successfully integrated into clinical practice, delivering the web-based self-help intervention to individuals in need of services may alleviate the high burden of BED for patients, their families, and society.

## Abbreviations

APAAmerican Psychiatric AssociationAPOIAttitudes Towards Online InterventionsAZAktenzeichen [File number]BEDBinge Eating DisorderBMIBody Mass IndexBPtKBundespsychotherapeutenkammer [German national association of psychotherapists]CBTCognitive-Behavioral TherapyCIAClinical Impairment AssessmentCONSORTConsolidated Standards of Reporting TrialsCSSRIClient Sociodemographic Service Receipt InventoryDERSDifficulties in Emotion Regulation ScaleDSM-5Diagnostic and Statistical Manual of Mental DisordersDIPSDiagnostic Interview for Mental DisordersEDEEating Disorder Examination InterviewEDE-QEating Disorder Examination QuestionnaireEMAEcological Momentary AssessmentEUEuropean UnionGAD-7Generalized Anxiety Disorder Scale-7HFERSTHeidelberg Form for Emotion Regulation StrategiesICCIntraclass Correlation CoefficientICD-11International Classification of Diseases, Eleventh Revision*i*PCQProductivity Cost QuestionnaireLOCFLast Observation Carried ForwardMICEMultiple Imputations by Chained EquationsMLMMultilevel Modeling*i*MTAInstitute for Medical Technology AssessmentNEQNegative Effects QuestionnairePATHEVPatients' Therapy Expectation and Evaluation ScalePHQ-9Patient Health Questionnaire-9PICOPopulation Intervention Compared OutcomeRSESRosenberg Self-Esteem ScaleSPIRITStandard Protocol Items: Recommendations for Interventional TrialsWBQWeekly Binges QuestionnaireWHO-5World Health Organization-Five Well-Being Index

## Trial status

Recruitment started in January 2021 and is still ongoing. The first patient was enrolled in the study on January 15th, 2021. Assessments are expected to be completed by May 2022.

## Ethics approval and consent to participate

Ethics approval has been obtained from the institutional review board at Heidelberg University (AZ Tim 2020 1/1). Informed consent will be obtained from all participants, and the trial will be conducted in compliance with the Declaration of Helsinki and good clinical practice. International data privacy regulations and EU legislation will be considered.

## Availability of data and material

The de-identified and anonymized data and the R analysis script of the current trial will be made available on the *Open Science Framework* (https://osf.io/pknbz/?view_only=9a0c786764bb4552b52be685a51220af).
